## Abstract

**Simple Summary:**

Following injury, players may seem medically fit to return to play, but skill levels may have deteriorated due to cognitive decline, resulting in the deterioration of cognitive abilities and skills. This suggestion may explain in part the reoccurrence of head injury linking concussive events to future concussive events. As such, this study’s aim will be to investigate performance and physiological changes in rugby players post-game for head trauma and injury.

**Abstract:**

Background: Taking part in moderate-to-vigorous exercise in contact sports on a regular basis may be linked to an increase in cerebrovascular injury and head trauma. Validated objective measures are lacking in the initial post-event diagnosis of head injury. The exercise style, duration, and intensity may also confound diagnostic indicators. As a result, we propose that the new Interdisciplinary Group in Movement & Performance from Acute & Chronic Head Trauma (IMPACT) analyze a variety of functional (biomechanical and motor control) tests as well as related biochemistry to see how they are affected by contact in sports and head injury. The study’s goal will be to look into the performance and physiological changes in rugby players after a game for head trauma and injury. Methods: This one-of-a-kind study will use a randomized controlled trial (RCT) utilizing a sport participation group and a non-participation control group. Forty male rugby 7 s players will be recruited for the study and allocated randomly to the experimental groups. The intervention group will participate in three straight rugby matches during a local 7 s rugby event. At the pre-match baseline, demographic and anthropometric data will be collected. This will be followed by the pre-match baseline collection of biochemical, biomechanical, and cognitive-motor task data. After three consecutive matches, the same measures will be taken. During each match, a notational analysis will be undertaken to obtain contact information. All measurements will be taken again 24, 48, and 72 h after the third match. Discussion: When the number of games increases owing to weariness and/or stressful circumstances, we expect a decline in body movement, coordination, and cognitive-motor tasks. Changes in blood biochemistry are expected to correspond to changes in biomechanics and cognitive-motor processes. This research proposal will generate considerable, ecologically valid data on the occurrence of head trauma events under game conditions, as well as the influence of these events on the biological systems of the performers. This will lead to a greater understanding of how sports participants react to exercise-induced injuries. This study’s scope will have far-reaching ramifications for doctors, coaches, managers, scientists, and sports regulatory bodies concerned with the health and well-being of athletic populations at all levels of competition, including all genders and ages.

## 1. Introduction

Sports-related concussion (SRC) diagnosis is encumbered by a lack of validated, objective diagnostic tests [1]. Currently, the Sport Concussion Assessment Tool-5th edition (SCAT5) [2] is the standard instrument used to diagnose SRC at the side-line and pitch side of athletic and sporting events. However, research has suggested that exercise is a confounding variable not accounted for when using the SCAT5 [3,4]. This is concerning because the baseline SCAT5 is typically administered under resting conditions but is used to diagnose SRC following physical exertion during and after sports activity. In addition to the SCAT5, biochemical biomarkers have been suggested as objective markers to aid in SRC diagnosis. Similar to the SCAT5, potential SRC diagnostic biomarkers may also be confounded by exercise. Therefore, a particularly important goal of this study is to examine several biomechanical tests, motor control tests, and biomarkers to investigate whether they are influenced by contact in sports and the prevalence of injuries to the head. This will be achieved by investigating movement and coordination tests, cognitive tests, visual tests, and a variety of blood-based biomarkers prior to and after rugby match performance, with the specific aim of investigating performance degradation.

The blood-based biomarkers included in the analysis and evaluation will include protein S100B (S100B), creatine kinase (CK), cardiac troponin T (CTT), cortisol (C), neuron-specific enolase (NSE), brain-derived neurotrophic factor (BDNF), glial fibrillary acidic protein (GFAP), and ubiquitin carboxyl-terminal esterase L1 (UCHL1). Protein S100B has been shown to increase after a concussion [5,6,7], following punches and kicks to the head in boxing [8] and karate [9], after playing a contact sport [5,7,10,11,12,13,14,15,16,17,18,19,20,21], and after exercise [22,23,24,25,26,27,28]. Past research has shown that S100B can be used as a marker of brain injury since this protein is housed in the astrocytes; however, its ability to diagnose SRC appears to be confounded by exercise since S100B is also located in skeletal muscle [29]. Creatine kinase will be measured as an indicator of skeletal muscle damage [30] to aid in distinguishing S100B release caused by skeletal muscle injury.

Although cardiac troponin is typically used as an indicator of myocardial injury [31], it has also been shown to predict mortality rates from brain trauma in clinical environments [32,33,34]. Cardiac troponin will be investigated as a potential cardiovascular damage marker in rugby athletes. We expect minimal nonclinical elevations in cardiac troponin levels post-exercise as a result of exercise intensity and not cardiac pathology [35]. Cortisol is a biomarker related to stress that increases as a result of head injury [36] and also in response to head contact during boxing [8]. However, cortisol has not been shown to increase in contact sports in the absence of SRC [10,37]. Whether cortisol increases because of rugby play in the absence of SRC will be a partial focus of investigation in this study.

Neuron-specific enolase provides a diagnostic indication of brain trauma and has been shown to increase post-match in boxers [8,38], karate practitioners [9], soccer players [18,19], and American football players [10]. However, the use of NSE as a brain trauma biomarker has been questioned due to the absence of significant NSE increases in post-game hockey [20], as well as in concussed hockey players [12]. Measuring NSE pre- and post-rugby matches will help distinguish whether NSE consistently increases due to playing a contact sport in the absence of SRC. Furthermore, it is necessary to consider the implications of increased exercise on cognitive function and brain health.

Exercise has been shown to improve memory and cognitive function [39]. These improvements are possibly related to the increase in BDNF caused by exercise training. BDNF is important in neuronal growth and maintaining synaptic connectivity in the brain [40]. Since BDNF plays a critical role in brain health, it may be beneficial for BDNF to be up-regulated following brain injury to enhance recovery. However, there is a paucity of research on BDNF concentrations after brain injury. To date, there have been three studies investigating BDNF in brain injury, and all were performed on children [41,42,43]. One indicated that BDNF increased after a concussion in children [41], with the other two studies observing mixed results, with BDNF levels increasing in correlation with the severity of the brain injury [42,43]. A single bout of exercise has been shown to increase serum BDNF levels in sedentary subjects [44,45], recreationally active subjects [46,47], and trained cyclists [48,49], but increases in serum BDNF after a contact sport in trained athletes have not yet been investigated. GFAP and UCHL1 will be investigated, as these two proteins have been shown to distinguish between computed tomography (CT)-positive and CT-negative brain injury [50] and have been approved for use in the assessment of mild traumatic brain injury (mTBI) [51]. There is clearly a need to compose a test batch for the assessment of brain health.

In order to consider how to determine the most sensitive and specific test for the symptoms of SRC, we propose that an interdisciplinary approach would be powerful in determining the levels of changes in the biological system, where the dynamics of change are consistently present. Changes in cognitive, visual, and movement functions are symptoms of SRC, and it has been suggested that the multimodal assessment of these has better sensitivity than balance or cognitive tests alone [52]. For example, based on elements of the SCAT5, short-term memory, balance, and symptom severity are rated. However, while the test-retest reliability of the SCAT5 as a whole is reported to be moderate to high, the reliability coefficients of SAC and mBESS (rs = 0.58 and 0.40, respectively) are low [53]. Partly, this is suggested to be due to individual variability and the interval-scale scores of the tests. However, currently, there are no quantitative tests for cognitive, visual, or movement function included in the SCAT5, which limits the generation of precise numerical values that can be used to identify and characterize symptoms of SRC.

Executive function has been examined in line with neurological conditions [54] and is relevant to the study of acute and chronic effects of head trauma [55,56,57]. Executive function and its relationship with decision making based on specific environmental cues that underpin motor behaviors are key in sports performance and injury risk. Evidence linking concussive events to future concussive events [58] and twice the likelihood of obtaining another musculoskeletal injury [59] suggests that executive function and aspects of neuromuscular and movement functions are impaired after concussive incidents. However, there is a need to study the acute and chronic effects of mTBI/SRC individually, as well as holistic measures of body movement and coordination, to facilitate the identification of the most sensitive and specific indicators of injury and brain function.

Gross motor function tests are currently based on standing posture and gait, and these are tasks fundamental to daily activity. While technology-based data capture for balance control, such as the clinical measure of the mBESS, is being increasingly published, Buckley et al. (2018) highlight reliability and sensitivity issues [60]. These may be overcome with the use of sensor-based balance measures, particularly in the mediolateral direction [61]. Research exploring the effect of a concussion on walking gait presents conflicting conclusions. Manaseer et al.’s (2020) systematic review suggested that individuals who have had a concussion may wobble more in the frontal plane and walk slower than healthy controls [62]. Fino et al. (2018) agreed that the literature implies that gait is abnormal shortly after a concussion or mTBI, and that dual-task and complicated gait tests have special potential for detecting impaired locomotor function [63,64]. However, there is little agreement on the most important gait metrics for SRC diagnosis and therapeutic intervention. In addition, since locomotion is a fundamental motor skill that does not stress the motor control system of a healthy individual, even with dual-task paradigms, it might not be sensitive or specific enough to show changes in motor control function due to SRC in highly trained athletes. Therefore, we propose that a complex sports-specific skill that includes an element of decision making might be more effective for detecting changes in motor control function after SRC in sports players. The inclusion of an ecologically valid throwing task captured using automated motion capture with synchronized external force plates will facilitate the subsequent quantification of joint and segmental kinematics and kinetics and will allow insights into changes in coordination patterns and joint moments and power. This study will provide the first evidence of the effect of head injury on the technique of performing a sports-specific gross motor skill.

In order to understand the facets of motor control function that may underpin changes in the performance of gross motor skills, it is important to perform a number of tests of executive function and specific aspects of perception-action coupling. For example, reaction time is a promising indicator of visuo-motor deficits following SRC [65], which is quick and easy to quantify. Finger-tapping and fine motor skill tasks (f/e the Perdue Pegboard test) [66,67,68,69] have been used widely in cognitive psychology to identify neurological conditions. In order to understand the facets of motor control function that may underpin changes in the performance of gross motor skills, we will perform a number of perception-action and physical tasks. Specifically, we will explore reaction time, executive function (Stroop word test), and fine motor skills (finger tapping and Perdue Pegboard).

The study’s aim, therefore, is (1) to examine changes in biomarker concentrations and biomechanical and cognitive-motor abilities of elite rugby players across three-match tournaments until 72 h after the final game and (2) to explore the relationship between subconcussive head impacts and their intensity and changes in blood biomarker concentrations, biomechanical tasks, and cognitive-motor tasks.

It is hypothesized that (1) the whole-body movement, coordination, and cognitive-motor tasks will decrease significantly with the duration of games played because of fatigue and/or concussive events; (2) blood biomarkers (i.e., CK, cardiac troponin T, NSE, S100B, BDNF, GFAP, and UCHL1) will increase significantly after rugby tournaments; (3) a correlation will be explored between the number of head impacts (quantified with a notational analysis) and the aforementioned indicators. The study has been registered as a clinical trial (clinicaltrials.gov NCT04841876 (assessed on 16 March 2022)) and has been approved by the Research Ethics Committee of Hong Kong Baptist University (REC/20-21/0452).

All data collection, including motor control, biomechanics, and blood analyses, will be performed through formal collaboration with the universities constituting the Sport and Health Interdisciplinary Group in Movement & Performance from Acute & Chronic Head Trauma (IMPACT) research group based at Cardiff Metropolitan University. Funding for this project will be covered by the institutes involved.

## 2. Materials and Methods

### 2.1. Study Design and Participant Recruitment

This study will be a randomized control trial. The study will consist of two groups: one sport-event group (SG) and one control group (CG); see Figure 1.

Sample sizes were calculated using G*Power 3.1 software (Heinrich-Heine-University Dusseldorf, Dusseldorf, Germany). Calculations were based on a previous study [7], and we aimed to achieve a substantial effect size of 0.8 (Cohen’s d) on blood biomarkers. With an alpha of 0.05 and a power of 80%, 40 participants (20 participants per group) are required to achieve a robust estimation of the relevant parameters. All participants will be required to be over 18 years of age to participate in the study. Prior to data collection, all participants will be fully familiarized with testing procedures and the laboratory environment. In addition, a pilot study will be performed prior to actual experimental data collection. This will provide valuable information concerning timing, standardization, subject preparation, data collection information, logistics, and experimental organization in terms of data management for all participants pre- and post-testing. Members of the research team supervising each different aspect of data collection will ensure the standardization and integrity of data collection. Blood samples will be collected at several phlebotomy locations to ensure bloodletting is performed immediately post-match. There will also be several locations provided by the research team to collect biomechanical and cognitive-motor task data. These multiple locations will enable efficiency and effectiveness in data collection post-event, minimizing the effect of time as a confounding variable.

All the recruited participants will be male rugby 7 s players based at Cardiff Metropolitan University. Inclusion criteria will be participation in rugby 7 s tournaments for a minimum of 2 years and free from injury. After agreeing to participate in this study and passing the eligibility assessment, the participants will sign informed consent forms outlining the experimental design and procedures and will then be randomly assigned to SG or CG in a ratio of 1:1. The control group will comprise 7 s rugby players who are part of the 7 s squad but will not be participating in the actual rugby competition. Therefore, they will be injury- and fatigue-free, and direct comparisons will be possible to investigate the effect of games and contact on sports performance. In addition, baseline measures will also be useful in determining any changes within and between groups. This will enable meaningful comparisons between groups that are sport-specific. Both groups will participate in baseline and post-match data collection. Randomization will be conducted using the random function available in Excel software. All participants will be asked to maintain their regular training and dietary habits during the testing period. The participants will also be required to record their exercises and food intake for 24 h prior to each blood sampling. 

Baseline testing will include measures of (1) demographics, (2) blood, and (3) biomechanical and cognitive-motor tasks and will be conducted on the day before the tournament. The information on the tournament play of each participant in SC, i.e., approximate playing time, number of matches played, and time that the last match was finished, will be recorded and used as the time markers of post-match testing. Post-match testing, including blood and biomechanical and cognitive-motor tasks, will be performed immediately after each game and three times after the third game at 24, 48, and 72 h (Figure 1, Table 1). All data will be collected at the Human Performance Laboratory at Cardiff Metropolitan University. The same order of testing will be standardized for all players based on pilot study results. All experimental data collection will take place immediately post-game for all three matches. Players will report to the laboratory located pitch side for all blood, biomechanical, and cognitive data collection. Once data collection has finished, players will be told to shower and relax. The players will then be asked to return to the laboratory at 24, 48, and 72 h after the tournaments for repeated blood measurements and biomechanical and cognitive-motor tasks. There will be no physical activity during this post-activity testing period.

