### 2.5. Statistical Analysis

Data will be analyzed using IBM SPSS 26.0. Diagnostic testing (e.g., outlier detection, distribution examination, homogeneity checking) will be conducted for all data, and all skewed values and missing values will be addressed using a multiple imputation approach. To examine the differences between the baseline and the testing days for each of the physiological, cognitive-motor, and whole-body movement skills, a series of generalized linear mixed models will be employed, controlling for several demographic covariates. Post hoc tests will be performed using the Bonferroni procedure, Mann-Whitney U test, and Chi-square test for different types of data. The significance level will be set at 95% (two-tailed). The effect size of Cohen’s d will be calculated, with 0.3, 0.5, and 0.8 indicating small, medium, and large effect sizes, respectively.

Due to the difference in the type of data (discrete and continuous), a variety of methods will be employed, including statistical parameter mapping to examine continuous data between the four sessions and baseline. A canonical analysis will be used as a multivariate technique to determine the relationships between the variables and the selected performance of key dependent variables. All collected data will be anonymized and stored on a password-protected computer, with access only granted to the lead investigator.

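### The stated 80% power for 20 players per group does not follow from the stated inputs: an unadjusted two-tailed two-group comparison at d = 0.8 has 69% power

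*Protocol article*

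**What the plan says.** The sample-size paragraph in Section 2.1 of the protocol article reports that "Sample sizes were calculated using G*Power 3.1 software". The target is given as "we aimed to achieve a substantial effect size of 0.8 (Cohen’s d) on blood biomarkers", and the result is "With an alpha of 0.05 and a power of 80%, 40 participants (20 participants per group) are required". Players are "randomly assigned to SG or CG in a ratio of 1:1", so the two groups are equal in size. The paragraph names no test, no sidedness, no number of repeated measurements and no within-player correlation.

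Section 2.5 supplies the sidedness: "The significance level will be set at 95% (two-tailed"), which I read as a 5% level. It also describes the main analysis: "a series of generalized linear mixed models will be employed, controlling for several demographic covariates".

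**The concern.** Effect size, alpha, power, allocation and group size are all given, so the calculation can be checked. A standardised difference with a number per group most naturally describes a two-sample comparison of means. Under the two-tailed level of Section 2.5, that comparison does not give 20 per group.

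This is the only power statement in the article and the only justification for 40 players. If the true effect is d = 0.8 and the groups are compared without adjustment, the chance of missing it is 31% (100 − 69.3), not 20%. The study hypothesises rises in seven blood biomarkers. A reader who trusts the 80% would give non-significant results more weight as evidence of no effect than they deserve.

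**Working it through.** **Inputs.** d = 0.8, alpha = 0.05, target power 80%, n = 20 per group, 1:1 allocation (all Section 2.1); two-tailed (Section 2.5). The SD is 1 because d is standardised.

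**Formula.** For two independent groups of n, the t statistic has df = 2n − 2 and noncentrality δ = d·√(n/2). Two-tailed power is P(|T| > t(0.975, df)) and one-tailed power is P(T > t(0.95, df)), with T noncentral t.

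**1. Trying to reproduce the plan's figure, two-tailed.** At n = 20, δ = 0.8·√10 = 2.530, df = 38 and the critical value is 2.024. Power is **69.3%**. The normal approximation gives 71.6%. Neither is 80%.

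**2. Size needed, two-tailed.** 25 per group gives 79.1% and 26 per group gives 80.7%. The requirement is therefore 26 per group, 52 in total. The normal approximation gives 25 per group.

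**3. Detectable effect at 20 per group.** Solving for 80% power gives d = **0.91** (δ = 0.909·√10 = 2.87).

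**4. One-tailed variant.** With the same δ of 2.530 and a critical value of 1.686, power at 20 per group is **79.9%**. A strict search for at least 80% returns 21 per group (81.7%). The normal approximation returns 20 (81.2%). This comes very close to the stated figure but contradicts the two-tailed level.

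**5. Two-sided, baseline-adjusted.** If ρ is the correlation between baseline and post-match values, adjustment shrinks the residual SD by √(1 − ρ²). The effective difference becomes 0.8/√(1 − ρ²), with about 37 df. The article gives no ρ, so the values below are assumptions.

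| Assumed ρ | Effective d | Power at 20 per group |
|---|---|---|
| 0.3 | 0.84 | 73% |
| 0.4 | 0.87 | 77% |
| 0.48 | 0.91 | 80% |
| 0.5 | 0.92 | 81% |
| 0.6 | 1.00 | 87% |
| 0.7 | 1.12 | 93% |

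**6. Two-sided, repeated-measures between-group F-test.** With two equal groups, f = d/2 = 0.4. With m measurements at common correlation ρ and N = 40, the noncentrality is λ = f²·N·m/(1 + (m − 1)ρ), on 1 and 38 df. For m = 2 and ρ = 0.5, λ = 0.16·40·2/1.5 = 8.53 and power is **81.2%**. For m = 4, power is 88% at ρ = 0.5, 80% at 0.7 and 76% at 0.8. Again ρ is assumed. Here a higher correlation lowers power, whereas in step 5 it raises it.

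**The case against.** The strongest reply is that the trial is a repeated-measures study. Section 2.5 plans mixed models, not a t-test at one time point. Step 6 shows that a two-sided repeated-measures calculation can return about 80% at N = 40, and the calculation rests on a cited earlier study that is not at hand. On this view the 80% is poorly documented but not wrong.

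Part of this stands, and it rules out two stronger readings. A reader might infer that the power claim is false for the analysis the trial will actually run. The article does not support that: the planned mixed models could have more power than the unadjusted test, so 69% and 52 players hold only for the unadjusted comparison. A reader might also infer that only a one-tailed test could have produced 40. Steps 5 and 6 show that other routes lead there too, and an exact one-tailed search gives 21 per group, not 20.

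The reply does not rescue the statement as printed. Its only effect measure is Cohen's d with a number per group, and no correlation or number of measurements enters it. The covariates that Section 2.5 names are demographic; it does not say that baseline biomarker values are adjusted for. The rescue also depends on the correlation chosen: step 5 falls short of 80% at 0.4, and step 6 with four measurements falls short at 0.8. Step 6 further requires the 0.8 difference to be present, on average, across all the measurements counted, which a pre-match sample in randomised groups would not show.

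A reader might add that no allowance is made for players lost to injury. That is a detail an article may leave to the full protocol, and it forms no part of this point.

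**Conclusion.** The concern holds in conditional form. From the article's stated d, alpha, group size and two-tailed level, an unadjusted two-group comparison of means has 69.3% power, about 11 percentage points below the stated 80%. That comparison would need 26 per group, six more than planned, or a true d of 0.91.

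At 40 players, about 80% can be reached in two ways. One is a one-tailed test, which conflicts with Section 2.5. The other is a two-sided analysis using baseline or repeated values under a correlation that the article does not give. The stated power is therefore unsupported by its own inputs, although it is not shown to be unattainable for the planned mixed models.

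The figures assume normally distributed outcomes with equal variances, a single biomarker at a single comparison, and complete data on 20 per group.

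**What to change.** Make two changes to the text of Section 2.1, consistent with the two-tailed level in Section 2.5.

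1. Replace the power sentence with wording such as: *With 20 players per group and a two-tailed alpha of 0.05, an unadjusted comparison of the two groups has 69% power for d = 0.8; 80% power is reached at d = 0.91.*
2. Name the baseline-adjusted difference between the sport-event and control groups as the powered comparison, using the baseline bloods already collected in both groups. State the assumed baseline-to-post correlation with its source, and show the range: 77% power at 0.4, 80% at 0.48, 81% at 0.5 and 93% at 0.7. The value 0.48 is simply the point at which 80% is recovered. It should not be adopted as the planning assumption unless pilot or published data support it.

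If the original calculation used a repeated-measures procedure, report its number of measurements and its correlation instead. If it was one-tailed, reconcile it with Section 2.5.

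The cost is a few sentences and a less favourable headline figure. No additional players or measurements are needed.

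### The activity rules after the matches contradict each other, and the comparison with non-playing controls estimates match participation, not contact by itself

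*Protocol article*

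**What the plan says.** **Activity.** Section 2.1 of the protocol article gives two rules. The first is for everyone: "All participants will be asked to maintain their regular training and dietary habits during the testing period". The second follows the description of the visits at 24, 48 and 72 h: "There will be no physical activity during this post-activity testing period". Neither rule refers to the other. The sentences just before the second speak of players who finish match-day testing and come back. The same section says that both groups take part in baseline and post-match data collection, and that participants log exercise and food for the 24 h before each blood sample.

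**Control condition.** Controls are members of the same squad who do not play in the tournament. Section 2.1 draws this conclusion: "Therefore, they will be injury- and fatigue-free, and direct comparisons will be possible to investigate the effect of games and contact on sports performance".

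**Aim.** The Introduction sets the goal of examining biomechanical tests, motor control tests and "biomarkers to investigate whether they are influenced by contact in sports and the prevalence of injuries to the head". It also warns that "potential SRC diagnostic biomarkers may also be confounded by exercise", and says of S100B that "its ability to diagnose SRC appears to be confounded by exercise since S100B is also located in skeletal muscle". Hypothesis 1 expects decline "because of fatigue and/or concussive events". Hypothesis 3 is a correlation, to be explored, between the number of head impacts and the outcomes.

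**Analysis.** The mixed models in Section 2.5 control for demographic covariates. No exertion measure is named. CK is measured to help identify S100B that comes from muscle.

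**The concern.** Two separate problems arise.

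1. Exertion between 24 and 72 h is not defined. CK is the protocol's marker of muscle damage, and the Introduction cites studies in which S100B rises after exercise. If one arm trains and the other rests, the group difference at those visits contains a difference in training that has nothing to do with the matches.

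2. SG and CG differ in running, match stress and contact all at once. A clear group difference therefore cannot say whether contact contributed, although the Introduction makes contact a goal and names exercise as the confounder. The within-SG relation to impacts could speak to this, but players who are on the pitch longer and run more are likely to have more collisions. A plain correlation would carry that exertion signal with it.

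The second problem comes from the non-playing control and would remain however the activity rules were settled.

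**Working it through.** **Activity rules, by reading**

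- If the no-activity rule covers everyone, it contradicts the instruction to maintain training.
- If it covers only the returning match players, SG rests while CG may train, and exertion differs by arm.
- If it is a narrower exception to a general rule, the text does not say so or say which arms it binds.

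**The plan's own figure.** Section 2.1 gives d = 0.8, alpha 0.05, power 80% and 20 per arm. By the normal formula, n per arm = 2(z_alpha + z_beta)²/d².

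- One-sided: 2(1.645 + 0.842)²/0.64 = 19.3, so 20 (21 with the t distribution).
- Two-sided, as Section 2.5 states: 2(1.960 + 0.842)²/0.64 = 24.5, so 25 (26 with t).

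The stated 40 matches the one-sided calculation. That is a separate matter; here it only fixes the starting power. With 20 per arm, two-sided 0.05, t-based, power at d = 0.8 is 0.693.

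**Size of the follow-up bias (assumed shifts).** Suppose the true SG minus CG difference at a follow-up visit is 0.8 SD and training raises the CG mean by s SD. The observed difference is 0.8 − s.

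| s (assumed) | Observed difference | Power, 20 per arm |
|---|---|---|
| 0 | 0.8 | 0.693 |
| 0.2 | 0.6 | 0.456 |
| 0.4 | 0.4 | 0.234 |

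**What the group contrast can show.** Suppose contact has no effect and exertion alone shifts SG by d (assumed). The chance of a significant group difference is 0.095 at d = 0.2, 0.338 at d = 0.5 and 0.693 at d = 0.8. Such a result would be correct for match participation and uninformative about contact.

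**The plain head-impact correlation (assumed inputs).** Suppose an outcome depends only on running load, with correlation 0.5, and impact count correlates 0.5 to 0.7 with load. The unadjusted correlation of impacts with the outcome is the product:

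- 0.5 × 0.5 = 0.25
- 0.7 × 0.5 = 0.35

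The numerator of the load-adjusted partial correlation is 0.25 − 0.5 × 0.5 = 0, and 0.35 − 0.7 × 0.5 = 0, so adjustment removes it. For scale, with 20 players a correlation reaches two-sided 0.05 at about 2.101/√(2.101² + 18) = 0.44. The spurious value alone would usually fall short of that, but it would be added to any real association.

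**Price of adjustment.** Variance inflation for one covariate is 1/(1 − r²):

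- r = 0.5: 1/0.75 = 1.33
- r = 0.7: 1/0.51 = 1.96

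Interval width grows by the square root, 1.15 to 1.40 times. This holds residual variance fixed. If load explains part of the outcome, the net cost is smaller.

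**Which exertion measure.** Section 2.1 records playing time, and Section 2.3.2 collects high-speed running and GPS data on speed and distance. Body load in Section 2.3.2 sums accelerations, changes of direction and impacts, so adjusting for it would remove part of the contact signal.

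**The case against.** - **The group comparison is honestly described.** The quoted sentence in Section 2.1 speaks of games and contact together, and a randomized non-playing control can estimate that combined effect. Hypothesis 1 and the Discussion allow fatigue or exercise as causes. This stands. A reader might infer that the plan attributes the group difference to contact alone; the text does not say so.
- **Some separation is planned.** CK is measured to identify S100B of muscle origin, head impacts are to be correlated with the outcomes, collisions and high-speed running are coded, impacts are graded by zone, and Section 2.5 plans a canonical analysis. A reader might infer that nothing planned bears on the question; that would be wrong. What remains is that CK bears only on the muscle source of S100B and that the impact relation is stated without adjustment. An analysis plan not shown here may add covariates, but the control condition, the goal on contact and the plain correlation are in this text.
- **The activity rules could be a general rule and a later exception.** This is possible, but not stated, and it would still leave open whether controls are bound by the exception.
- **The test battery.** A reader might see the sprints and tackles in the tests as a further breach of the no-activity rule, or as a source of bias. Both groups take part in post-match testing, so the tests load both arms alike. It is also strained to read the rule as excluding the study's own tests, and Table 1 does not list the tackle task.
- **The sizes are assumed.** This stands. The document gives no training effect, exertion effect or correlation between contact and load.

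**Conclusion.** Both points hold as limited here. The two activity rules in Section 2.1 conflict and must be reconciled. Under one natural reading they let exertion differ by arm from 24 to 72 h. If controls train and players rest, the likely direction is to understate the SG excess in CK and S100B. The size is unknown: at assumed control shifts of 0.2 to 0.4 SD, power for a true 0.8 SD difference falls from 0.69 to between 0.46 and 0.23.

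The SG minus CG contrast is a valid estimate of match participation and cannot alone answer the Introduction's question about contact. The head-impact correlation, as stated, would pick up 0.25 to 0.35 from running load under the assumed correlations. This calls for a change of instruction, interpretation and one analysis. It does not invalidate the randomized comparison.

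**What to change.** 1. Reconcile the two activity statements in Section 2.1 into one instruction, applied identically to SG and CG through 72 h. Which rule to keep is for the investigators. Check adherence by arm with the exercise record: 24 h before each of the 24, 48 and 72 h samples covers the whole follow-up.
2. State that SG minus CG estimates the effect of match participation, exertion plus contact.
3. Replace the plain correlation with a regression within SG of the baseline-adjusted outcome on contact or head-impact count, adjusted for one exertion measure already collected: playing time, or GPS distance or high-speed running, but not body load. Name the measure in advance and report the result as exploratory, since impacts are not randomized.
4. Show S100B with and without CK as a sensitivity analysis only. Collisions may themselves raise CK, so adjustment could remove part of a contact effect.

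No new data are needed. The cost is a revised participant instruction, some analysis wording, and lower precision: variance about 1.3 to 2.0 times for one covariate at assumed correlations of 0.5 to 0.7. With about 20 SG players, adding several exertion covariates at once would cost more, which is why only one is proposed.
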